#### Secondary Outcomes Analyses

We hypothesize that fewer women who receive the intensive telephone intervention will require a repeat telephone intervention in subsequent years compared to women receiving the brief intervention. For this analysis we will assemble two cohorts of women, one that received ETTC and subsequently received a mammogram within 12 months of the call and another that received a reminder call (RC) and also received a mammogram within 12 months of the call. Proportions scheduling a mammogram within 18 months of the index mammogram and completing a mammogram within 19 months of the index mammogram will be compared between the two intervention arms.

The second hypothesis is that more women who schedule a mammogram after intensive counseling than after a brief reminder call will complete the mammogram. Other secondary analyses will include: 1) analysis of immediate term outcomes (change in stage of readiness, mammography scheduling) and short term outcomes (receiving a mammogram within three months) following telephone interventions, for all women receiving the interventions for the first time, adjusted as needed by appropriate covariates (e.g. age, time to last mammogram, marital status and other factors), 2) response to reminder letters measured by the proportion of women without a recent mammogram scheduled or completed who schedule a mammogram within two weeks of a reminder letter, compared to the proportion of women scheduling during other two week intervals, adjusted for age, time to last mammogram, and other factors as appropriate.

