### Interventions

Only women ≥ 18 months from a mammogram receive study interventions. See Figure 2. When women are ≥ 18 months from their last mammogram, they all receive the same reminder letter. The letter is electronically signed by a woman's PCP and states: 1) there is no record of a mammogram in the last 18 months, 2) getting regular mammograms every 1-2 years is important and 3) her PCP recommends that she call the Study Scheduler for a mammogram appointment. When women call, the Study Scheduler uses the same script for all, except as noted below for women in the counseling arm. (See Table 2 for Study Scheduler Protocol)

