#### RC Arm (reminder letter followed by Study Scheduler call)

All women receive a reminder letter as above. If a woman *does not call *following receipt of the reminder letter or does not schedule a mammogram on her own within two weeks of the reminder letter, the Study Scheduler makes up to five call-attempts to reach her. The script is the same as noted above.

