#### ETTC Arm: (reminder letters and booklet followed by Counselor call)

All women receive a reminder letter as above. If a woman calls following receipt of the reminder letter, the Study Scheduler uses the same script as in Table 2 but replaces item #4 with "Inform the woman that she will receive a mammography booklet but will not get a Counselor call unless she would like to". If a woman calls in to schedule or confirm a mammogram appointment that is inappropriately far in the future, the Scheduler sends a mammography booklet and makes an appointment for her to receive a Counselor call.

If after receiving the reminder letter, a woman schedules a mammogram on her own, there is no further intervention. If a woman in the counseling arm does not call within two weeks after the first reminder letter, a mammography booklet is sent with a second reminder letter that states that if she does not call or schedule a mammogram within two weeks, a Counselor will call her. If the woman does not respond to the second reminder letter, the Counselor will make five call-attempts.

Counseling calls typically last about 30-35 minutes. If a subject requires a repeat counseling call during the study period, the call content will be different from that of the initial call. During repeat calls, the Counselor will address any change in the subject's stage of readiness, beliefs and barriers. The Counselor protocol using the CATI (computer assisted telephone interviewing) system was detailed in our previous publication [44,45].

Theoretical Basis of the Counseling Intervention:

1. Our counseling script incorporates a stage-based theory of behavior change that emphasizes the evolution of knowledge and personal risk perception in the development of an intention to act, and the variables that then influence acting on that intention [46,47]. The stage-based models have attempted to integrate the conceptual bases and empirical findings of the older models of change to capture the complexities of health behavior. The Precaution Adoption Process Model (PAPM) [48,49] is useful in working with non-adherent women because it classifies them into four stages that provide a more detailed description of the earlier stages of decision-making. In designing the ETTC counseling algorithm, we used our pilot mammography study to adapt the PAPM stages (See Tables 3 &4) [44,45].

**Table 3 T3:** Staging A Woman's Readiness to Get A Mammogram

STAGE	PAPM STAGES REVISED

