### Data Collection and Management

During the four-year intervention period the claims database and the electronic health record data base are searched weekly to determine eligibility of women to receive a reminder letter. Study staff enter data on study enrollment when they receive information from PCPs and/or from women relevant to enrollment. The only data required for primary outcome measures on women enrolled in the study are duration of enrollment in FCHP/FC, dates of mammograms, and birth date for developing age-specific outcomes.

Secondary analyses will include subgroup analyses involving the primary outcome, analyses involving secondary outcomes (e.g. change in stage of readiness from beginning to the end of reminder and ETTC calls, completion of scheduled mammograms and time from intervention to mammogram completion) and other analyses requiring independent variables collected from the FCHP database and during all calls from and to subjects. Medicare and Medicaid insurance coverage, history of claims for preventive checkups and other screening tests (e.g. Pap smears, cholesterol, colon cancer screening) will be obtained from FCHP claims databases and the electronic health record database to compare adherence to mammography recommendations to the utilization of other preventive services. (Table 5 shows all of the data sources)

**Table 5 T5:** Data Sources for Analysis

Data Sources	Primary Outcome Analysis	Secondary Data Analyses	Process Analysis
FCHP and FC Membership Database	X	X	X

FCHP Claims Database and Electronic Health Record database	X	X	X

Fallon Clinic Scheduling System		X	X

Patient Survey (Administered to subjects calling the Study Scheduler or receiving reminder or ETTC calls)		X	

ETTC and Reminder Call CATI System & Tracking Database		X	X

Phone Call Logs			X

PCP Approvals for Patient Enrollment	X	X	X

Patient Refusals of Enrollment	X	X	

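### The 19-month completion measure runs into the repeat-intervention cycle that starts at 18 months and is not tied to appointments made before it

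*Protocol article*

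**What the plan says.** The Secondary Outcomes Analyses section hypothesizes that "fewer women who receive the intensive telephone intervention will require a repeat telephone intervention in subsequent years", compared with women given the brief call. The cohorts are women who had a mammogram within 12 months of an ETTC or RC call. Two proportions are then compared. One is "Proportions scheduling a mammogram within 18 months of the index mammogram". The other is introduced in the same sentence: "completing a mammogram within 19 months of the index mammogram will be compared between the two intervention arms". The sentence does not say that the completions must come from appointments made by 18 months, or that the woman must not have been contacted again.

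The timing of renewed contact is set elsewhere in the article:

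- Interventions, all arms: "When women are ≥ 18 months from their last mammogram, they all receive the same reminder letter".
- RC Arm, for a woman who has neither called nor booked: "within two weeks of the reminder letter, the Study Scheduler makes up to five call-attempts to reach her".
- ETTC Arm, first step, for a woman who "does not call within two weeks after the first reminder letter, a mammography booklet is sent with a second reminder letter". That second letter warns that "if she does not call or schedule a mammogram within two weeks, a Counselor will call her".
- Data Collection and Management: the claims database and "the electronic health record data base are searched weekly to determine eligibility of women to receive a reminder letter".

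The section on the proportion needing repeat interventions claims power above 85% for a 6-point difference, with 80% against 86% as its example.

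**The concern.** A measure of whether a woman needed a repeat intervention should be settled before that intervention starts. The 18-month scheduling proportion meets this test. The 19-month completion proportion, standing alone, does not, because its last month lies inside the repeat cycle.

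Take an RC woman who does nothing until the repeat call and is screened at 18.8 months. She counts as a success on a measure meant to show that she needed no call. An ETTC woman who was equally passive has not been called by then.

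Women who respond to the 18-month letter alone are less clear. The hypothesis speaks of a repeat telephone intervention, while the Outcomes and power sections speak of repeat interventions generally. Women who respond to the repeat call are misclassified on either wording.

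At stake is the interpretation of one component of a named secondary outcome.

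**Working it through.** **Inputs.** Letter at 18 months after the last mammogram (Interventions). RC call after 2 weeks without response (RC Arm). ETTC second letter and booklet after 2 weeks, counselor call after a further 2 weeks (ETTC Arm). Weekly eligibility search, so the letter may lag by 0 to 7 days (Data Collection and Management). Mean month = 365.25/12 = 30.44 days.

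**Timeline with no lag.**

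- RC call opens at 18 + 14/30.44 = 18.46 months.
- ETTC second letter and booklet: also 18.46 months.
- ETTC call opens at 18 + 28/30.44 = 18.92 months.
- The cut-off is 30.4 days after month 18.

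**Days of possible repeat calling before month 19.** RC = 30.4 − 14 − lag; ETTC = 30.4 − 28 − lag, set to 0 if negative.

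| Search lag (days) | RC call opens (months) | ETTC call opens (months) | RC days | ETTC days |
|---|---|---|---|---|
| 0 | 18.46 | 18.92 | 16.4 | 2.4 |
| 3.5 | 18.57 | 19.03 | 12.9 | 0 |
| 7 | 18.69 | 19.15 | 9.4 | 0 |

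The RC call opens before 19 months at every lag. The ETTC call passes 19 months once the lag exceeds 2.4 days. If status is fixed before the 18-month letter, both arms have 0 days.

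**The plan's power figure.** It cannot be reproduced, because the article gives no cohort size, alpha or sidedness for this comparison. Assuming two-sided alpha 0.05, 85% power for 80% against 86% needs 703 women per arm (736 with continuity correction).

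**Illustration only, not an estimate.** Assume 703 per arm and true need of 86% in RC and 80% in ETTC. Let x be the share of RC women needing a repeat who complete by 19 months because of the repeat call. Let y be the corresponding share of ETTC women responding to repeat contact. The apparent difference is 0.86(1 − x) − 0.80(1 − y).

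With y = 0:

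| x | Apparent difference (points) | Power |
|---|---|---|
| 0 | 6.0 | 85% |
| 1% | 5.1 | 72% |
| 2% | 4.3 | 55% |
| 3% | 3.4 | 38% |
| 5% | 1.7 | 13% |

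The difference vanishes at x = 1 − 0.80/0.86 = 7.0%.

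With y above 0:

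- x = 3%, y = 3%: 0.8342 − 0.7760 = 5.8 points, almost no change.
- x = 1%, y = 3%: 0.8514 − 0.7760 = 7.5 points, a shift in favour of ETTC.

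The documents give neither x nor y, so the direction of the net bias is not settled either.

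**The case against.** The strongest objection is that the two limits belong together: scheduled by 18 months, then completed within a one-month allowance. That would explain why they differ by a month. A woman first booked by the repeat call would then fail the criterion. Women who have already booked are not called, so the bias would largely disappear. This reading is plausible, but the article names two proportions and does not link them. If it is what was meant, the sentence should say so.

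Several stronger readings are tempting and do not hold.

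- A reader might infer that the ETTC call always falls after the cut-off. On the nominal schedule it can open about 2 days before month 19, although a mammogram completed in that time is unlikely.
- A reader might treat ETTC women as free of contact in the window. They receive a second letter and booklet when RC calling opens, and they can phone in to book. The imbalance concerns the telephone call only.
- A reader might put a size on the bias. If 30–50% of women were unscheduled at 18 months and 5–15% of these completed because of the RC call, the shift would be 0.30 × 0.05 = 1.5 to 0.50 × 0.15 = 7.5 points. The documents support none of these rates. The woman must be reached, booked and screened within 9 to 16 days, whereas the article's own short-term completion outcome allows three months.
- A reader might conclude that a true ETTC advantage would be hidden or reversed. The 18-month scheduling proportion tests the same hypothesis and is untouched, and the Outcomes section also lists the number of women requiring repeat interventions.

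It can also be said that any bias runs against the investigators' hypothesis and is therefore harmless. That is true of the call alone. It is not assured once ETTC responses to the letter and booklet are counted.

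**Conclusion.** The point holds in limited form. As written, the 19-month completion proportion overlaps the repeat cycle and can count women who responded to renewed contact as not needing it. Exposure to the repeat call inside the window is unequal: about 9 to 16 days in RC and 0 to 2 in ETTC. These figures follow from the article's own schedule, taking a lag of 0 to 7 days from the weekly search and calls that open as soon as each two-week wait ends.

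On the call alone the tendency favours RC. The net direction is uncertain and the size cannot be computed from the documents. The conclusion assumes that completion is a stand-alone proportion; if it is joint with scheduling by 18 months, little remains beyond a clarification. The scheduling proportion and the primary outcome are not affected.

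**What to change.** Amend the definition in Secondary Outcomes Analyses, identically for both arms:

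1. A woman needs no repeat if, before her 18-month letter is issued, she has completed a mammogram or holds a booked appointment.
2. Completions up to 19 months count only if they come from an appointment booked before that letter.
3. Actual receipt of a repeat call, taken from the tracking database, is reported as a supporting measure. This speaks directly to the telephone wording of the hypothesis.

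The cost is wording in the analysis definition. Table 5 already lists the scheduling system, the call tracking database and the claims and health-record data as sources for secondary analyses. The Blinding section defers outcome analyses to the end of the intervention phase, so the definition can be settled before results are known. One small drawback is that booking dates may be unavailable for mammograms at non-clinic sites. Those women would be classified by completion before 18 months.

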### Outcomes

The primary outcome is the proportion of women continuously enrolled for ≥24 months who have had ≥1 mammogram in the last 24 months. This measure mimics the standard HEDIS (Healthcare Effectiveness and Data Information Set) measure used by most health plans and systems to track mammography utilization, although the HEDIS measure is usually applied only to women age 50-69. The measure is a cross-sectional, prevalence measure that can be applied in a series of static "snapshots" to a dynamically changing population like the one in our study and in any typical health plan.

The secondary outcomes are 1) the number of women in each arm requiring repeat interventions and 2) the immediate outcomes (change in stage of readiness, mammography scheduling for those in the RC and ETTC arms during calls) and short term outcomes (receiving a mammogram within 3 months) following the interventions, for all women receiving the interventions for the first time, adjusted as needed by appropriate covariates (e.g. age, time to last mammogram, marital status and other factors).

The main cost-effectiveness outcome is the incremental cost-effectiveness of each intervention combination, that is, the difference in the percentage of eligible women with mammograms divided by the difference in total cost for each intervention pair. The study also measures separately the startup and operating costs of each intervention.

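### The three-month and completion outcomes are assessed among women called, or women who scheduled after a call; RC and ETTC women reach those groups by different routes, so contrasting the arms there is not a randomized comparison

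*Protocol article*

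**What the plan says.** The Secondary Outcomes Analyses section places the short-term outcome among women who received a call: "short term outcomes (receiving a mammogram within three months) following telephone interventions, for all women receiving the interventions for the first time". The same section states a hypothesis that compares the two call arms among schedulers: "more women who schedule a mammogram after intensive counseling than after a brief reminder call will complete the mammogram". Data Collection and Management lists "completion of scheduled mammograms and time from intervention to mammogram completion" among the secondary outcomes, so the time origin there is also the intervention.

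The Outcomes section describes the short-term outcome more widely: "short term outcomes (receiving a mammogram within 3 months) following the interventions, for all women receiving the interventions for the first time". That wording is not limited to calls and could include the letter-only arm.

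The routes to a call differ by arm:

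- **RC:** if the woman does not call in or "schedule a mammogram on her own within two weeks of the reminder letter, the Study Scheduler makes up to five call-attempts to reach her".
- **ETTC, main route:** two weeks without response to the first letter, then a booklet and second letter giving a further two weeks. After that, "If the woman does not respond to the second reminder letter, the Counselor will make five call-attempts".
- **ETTC, other routes:** a woman who phones in for an appointment too far ahead is booked for a Counselor call, and any woman who phones in can have one if she wishes.

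The adjustment named is for covariates as needed, with age, time to last mammogram and marital status as examples.

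**The concern.** The women in these denominators are chosen by what happened after randomization, and the choosing differs by arm. A woman who would act in the third or fourth week after the first letter can be in RC's called group. In ETTC the second letter and booklet may move her first, and she then leaves the called group. Conversely, some ETTC women who responded to the first letter enter the Counselor-call group by phoning in, while a similar RC woman gets only the Scheduler's brief message on her own incoming call. For the completion hypothesis there is a second filter: scheduling, which is itself a result of the call.

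The selection is on readiness to be screened, which is close to the outcome itself. Age, time since last mammogram and marital status cannot be relied on to remove it. At stake is the second study goal, which uses intermediate outcomes to improve the efficiency and sequencing of the interventions. The second letter and booklet are part of the ETTC sequence, and an analysis that drops the women they moved cannot judge that sequence.

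**Working it through.** The protocol gives no expected rate, sample size or power for the three-month or completion outcomes, so there is no figure to reproduce. The check sets the routes side by side and then asks how far selection alone could separate the arms. All response and screening probabilities below are assumptions.

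**1. Timing.** From the stated steps, the RC call comes about 2 weeks after the first letter and the main-route ETTC call about 2 + 2 = 4 weeks after it.

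**2. Simple illustration, identical calls, no call-in route.** Let a share e of two-week non-responders be about to act in weeks 3-4. They are screened with probability 0.9 and everyone else with probability 0.25 after either call. In RC they stay in the called group; in ETTC they leave it.

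- RC called-group rate = 0.9e + 0.25(1 − e) = 0.25 + 0.65e
- e = 5%: 28.3%; 10%: 31.5%; 15%: 34.8%; 20%: 38.0%
- ETTC called-group rate = 25%
- Spurious ETTC deficit: about 3 to 13 points

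**3. Two-class illustration, more moderate inputs, no call-in route.** A share w of women is ready and the rest reluctant. Each mailing draws a response with probability r (ready) or 0.03 (reluctant). After either call, the three-month mammogram probability is 0.60 (ready) or 0.15 (reluctant). Mailing responders are all counted as screened. Baseline results report 5,223 women eligible for intervention, so 5,223/3 = 1,741 per arm.

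- RC called: w(1 − r) ready and (1 − w)(0.97) reluctant
- ETTC called: w(1 − r)² ready and (1 − w)(0.97)² reluctant
- Called-group rate = (0.60 × ready + 0.15 × reluctant) / (ready + reluctant)
- Rate from the first letter = (1 − share called) + share called × called-group rate

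Worked case, w = 0.3, r = 0.4. RC: (0.180 × 0.60 + 0.679 × 0.15)/0.859 = 24.4%. ETTC: (0.108 × 0.60 + 0.659 × 0.15)/0.767 = 21.3%.

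| w | r | Called-group rate, RC / ETTC | Difference (points) | Chance a two-sided 5% test is significant | From first letter, RC / ETTC |
|---|---|---|---|---|---|
| 0.3 | 0.2 | 26.8% / 25.2% | −1.6 | 0.170 | 32.7% / 36.3% |
| 0.3 | 0.4 | 24.4% / 21.3% | −3.1 | 0.496 | 35.1% / 39.7% |
| 0.3 | 0.6 | 21.8% / 18.1% | −3.7 | 0.658 | 37.5% / 42.1% |
| 0.5 | 0.2 | 35.3% / 33.2% | −2.1 | 0.225 | 42.8% / 47.2% |
| 0.5 | 0.4 | 32.2% / 27.5% | −4.7 | 0.732 | 46.8% / 52.8% |
| 0.5 | 0.6 | 28.1% / 21.5% | −6.6 | 0.941 | 50.8% / 56.8% |

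With identical calls, the called-group comparison shows ETTC 1.6 to 6.6 points lower. From the first letter, the same model shows ETTC 3.6 to 6.0 points higher, because the second mailing is then credited to its arm.

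**4. Adding the call-in route.** In step 2, let a fraction f of ETTC's called group have phoned in, with screening probability q. The ETTC rate becomes 0.25 + f(q − 0.25), and ETTC minus RC is f(q − 0.25) − 0.65e. If q = 0.9 this is 0.65(f − e): a deficit when f is below e, an excess when f is above it. If q is below 0.25 the deficit grows. The protocol gives neither f nor q, so the sign is open.

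Neither illustration models completion among schedulers.

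**The case against.** The best case for the plan has four parts.

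- **Ranking the arms is the primary outcome's job.** That outcome is analysed by randomized arm among women enrolled at least 24 months and credits ETTC with its second letter and booklet. This stands.
- **The call analyses ask about mechanism.** Stage change during a call exists only for women called, and the three-month outcome carries no explicit RC-ETTC test; the contrast is only implied. This stands for those outcomes, but not for completion, where the ETTC-versus-RC hypothesis is explicit.
- **The clock.** Both arms get three months from their own call. A start about two weeks later is a minor matter beside the different composition of the groups, and the completion hypothesis has no window at all.
- **Covariates.** A reader might infer that adjusting for marital status discards letter-only women who never responded, because Table 5 ties the survey to certain women: "Patient Survey (Administered to subjects calling the Study Scheduler or receiving reminder or ETTC calls". Under the Secondary Outcomes Analyses wording those women are not in the analysis anyway. The loss arises only under the wider Outcomes wording, and marital status is only an example there.

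A reader might also infer that the comparison necessarily penalises ETTC. The documents do not support that: the ETTC Arm section sends some first-letter responders to a Counselor, and step 4 shows that this can reverse the sign.

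**Conclusion.** The point holds in a limited form. The among-called and among-scheduler groups are formed after randomization by different routes, so an RC-ETTC contrast within them is not a randomized comparison, and the named covariates cannot be relied on to make it one. The sign and size of the bias are unknown. The 2-to-13-point ETTC deficit rests on assumed response and screening probabilities, identical calls and no call-in route; it shows that the bias can be material and is not an estimate. The 0.17 to 0.94 chance of a false difference also assumes 1,741 women per arm. It would be wrong to infer that the trial's main result is compromised, since the primary outcome is unaffected. This is a change worth making to secondary analyses.

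**What to change.** Add a by-arm analysis that keeps the randomization. Take all women sent their first study reminder letter, which is the same in the three arms and comes before their treatment diverges. Compare by assigned arm the proportion with a mammogram scheduled, and the proportion with one completed, within one common period from the letter date. The period must cover ETTC's extra two weeks, the call attempts and three months. Four months is too tight: about 4 weeks to the ETTC call plus 13 weeks makes 17 of roughly 17.4 weeks. Six months (about 26 weeks) leaves about 9 weeks for call attempts. Adjust only for variables held on every woman: age, insurance, and time since last mammogram at the letter.

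Keep stage change, three-month outcomes among women called, and completion among schedulers as supporting analyses labelled non-randomized. Reconcile the Outcomes and Secondary Outcomes Analyses sections on which interventions the short-term outcome follows.

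The cost is some extra analysis work and rewording. Mammogram dates are already collected, and letters are triggered from the study's weekly database searches. The downside is that the by-arm result measures the whole outreach sequence, not the call alone, which is why the supporting analyses should stay.
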